## Abstract

**Background:**

In the United States, preterm birth (PTB) before 37 weeks gestational age occurs at an unacceptably high rate, and large racial disparities persist. To date, medical and public health interventions have achieved limited success in reducing rates of PTB. Innovative changes in healthcare delivery are needed to improve pregnancy outcomes. One such model is CenteringPregnancy group prenatal care (GPNC), in which individual physical assessments are combined with facilitated group education and social support. Most existing studies in the literature on GPNC are observational. Although the results are promising, they are not powered to detect differences in PTB, do not address the racial disparity in PTB, and do not include measures of hypothesized mediators that are theoretically based and validated. The aims of this randomized controlled trial (RCT) are to compare birth outcomes as well as maternal behavioral and psychosocial outcomes by race among pregnant women who participate in GPNC to their counterparts in individual prenatal care (IPNC) and to investigate whether improving women’s behavioral and psychosocial outcomes will explain the potential benefits of GPNC on birth outcomes and racial disparities.

**Methods/design:**

This is a single site RCT study at Greenville Health System in South Carolina. Women are eligible if they are between 14–45 years old and enter prenatal care before 20 6/7 weeks of gestational age. Eligible, consenting women will be randomized 1:1 into GPNC group or IPNC group, stratified by race. Women allocated to GPNC will attend 2-h group prenatal care sessions according to the standard curriculum provided by the Centering Healthcare Institute, with other women due to deliver in the same month. Women allocated to IPNC will attend standard, traditional individual prenatal care according to standard clinical guidelines. Patients in both groups will be followed up until 12 weeks postpartum.

**Discussion:**

Findings from this project will provide rigorous scientific evidence on the role of GPNC in reducing the rate of PTB, and specifically in reducing racial disparities in PTB. Establishing the improved effect of GPNC on pregnancy and birth outcomes can change the way healthcare is delivered, particularly with populations with higher rates of PTB.

**Trial registration:**

NCT02640638 Date Registered: 12/20/2015.

## Background

### Preterm Birth

It is well known that preterm birth (PTB) occurs at unacceptably high rates within the United States (U.S.), where 9.6% of babies were born preterm at less than 37 weeks gestational age in 2015 [1]. Large racial disparities persist, particularly between White and Black women; the latter had a 13.4% preterm birth rate in 2015 [1]. PTB is the leading cause of newborn death and disability. Moreover, the racial disparities in the newborn period have the potential to contribute to disparities in chronic disease, academic achievement and economic opportunity across the lifespan [2–4]. To date, medical and public health interventions have achieved limited success in improving rates of PTB. The causes of poor birth outcomes and health disparities are complex, involving biological, behavioral, psychosocial, socio-demographic, environmental, and medical factors [2]. Interventions that do not address these factors in a comprehensive way will have limited success.

Prenatal care has been the foremost strategy to improve pregnancy and birth outcomes in the U.S. Increasing access to individual prenatal care (IPNC) in the last twenty years has marginally improved rates of PTB, but has not made any headway in reducing racial disparities in birth outcomes [5–7]. Most IPNC appointments are short (10–15 min) and focus more on triaging medical risks, with limited time for psychosocial interventions or health promotion [8, 9]. Women are often referred to childbirth education or ancillary services to address these needs [10]. Deviation from recommended prenatal care content is associated with PTB and low birth weight (LBW), indicating the importance of prenatal care models that are structured to provide comprehensive content [11]. In addition, psychosocial factors during pregnancy (e.g. stress, anxiety, depression, and coping responses) are gaining increased attention as critical contributing factors to poor birth outcomes; however, the current IPNC model does not adequately consider these factors [12]. Innovative models in prenatal care that can address not only physical risk assessment, but also women’s psychosocial wellbeing are therefore highly desired.

### CenteringPregnancy group prenatal care model

The CenteringPregnancy group prenatal care (GPNC) model is distinctly different from the traditional practice of IPNC, requiring a paradigm shift in health care delivery for obstetric healthcare providers and fundamental changes to the patient-provider interaction. In this model, developed and trademarked by the Centering Healthcare Institute (CHI) (Boston, MA), groups of 8–12 women who are all due to deliver in the same month receive their medical care in a series of ten two-hour group sessions which take place through the second and third trimesters [13, 14]. The group sessions begin with patients measuring their own weight and blood pressure, followed by an individual physical assessment from a credentialed health care provider (either a physician or a nurse practitioner/midwife). Once these assessments are complete, the group meets together for structured discussion and activities that follow the curriculum developed by the CHI. Group sessions also include time for socialization, which encourages group members to develop relationships with one another. Group session topics are organized by relevancy to gestational age (Table 1). The model allows the provider to adapt the content according to the needs and priorities of the participants, with deviations from the curriculum noted to be addressed at a later session. Women are encouraged to bring a support person (e.g., boyfriend, husband, friend, family member) for group sessions. CHI has established a site training and annual certification process to assure consistency and quality in implementation for obstetric practices offering GPNC [15]. This model has been implemented in several hundred practices in the U.S. [15].

**Table 1 Tab1:** CenteringPregnancy group prenatal care (GPNC) curriculum outline

1	12–16 weeks	Prenatal testing, nutrition, healthy lifestyle choices	Exercise
2	16–20 weeks	Body changes in pregnancy, common discomforts, oral health	
3	20–24 weeks	Relaxation and stress reduction, breastfeeding	Gestational diabetes
4	24–28 weeks	Family relationships, violence and abuse, family planning, preterm labor	Breastfeeding
5	26–30 weeks	Labor, birth facility	Stress management/relaxation
6	28–32 weeks	The birth experience	
7	30–34 weeks	Newborn care	
8	32–36 weeks	Pregnancy to parenting transition, postpartum emotions, kick counts	Nutrition
9	34–38 weeks	Newborn safety, putting it all together	Preterm labor
10	36–40 weeks	Newborn care, growth and development, home and family changes	

There is promising evidence from both obstervational studies and radomized controlled trials (RCT) that suggests participation in GPNC is associated with reductions in preterm birth and low birth weight [16–19]. These findings have not been consistently reported in other studies [20–22]. The existing literature is limited by the small size of the previously randomized trials, as well as selection bias of the observational studies. Within this context, there is evidence that GPNC may result in reducing the racial disparity in preterm birth for Black women [16, 17]. Racial disparities in health have roots in inequalities in the provision of healthcare at the system level, the provider level, and the patient level. GPNC is designed to begin to address the racial disparities in all three levels. First, GPNC includes more patient-provider interaction time, with an average cumulative patient-provider interaction time of about 20 h throughout the pregnancy in GPNC, compared to 2 h for IPNC. More patient-provider interaction is believed to help develop the patients’ trust in their provider. Second, GPNC may reduce racial disparities in healthcare arising from unintentional prejudice and discrimination from healthcare providers, by allowing providers to develop a more robust understanding of patients’ family structures, social networks, employment or school, and physical home environment. Lastly, at the patient level GPNC is designed to promote goal setting and self-care of patients, empowering women to become more engaged in their health care and managers of their health by taking the responsibility for some of their health care.

### Current research gaps

Although this GPNC model has been successfully implemented in several hundred practices in the U.S., there are several significant gaps in the current literature. Existing studies are primarily observational studies that vary widely in quality, many of which are limited by self-selection bias and potential confounding [16, 18, 23, 24]. At the time we developed this proposal, only three RCTs had been published, but with mixed results. A secondary analysis of a study that was designed to examine GPNC’s impact on HIV risk behaviors and sexually transmitted infection demonstrated a 33% reduction in the odds of PTB in the GPNC group as compared with the control group [17]. The women in this study were younger than 25 years of age. A small trial in military settings did not find any significant difference in PTB or other birth outcomes [25]. The third trial in Iran also did not find any significant difference in PTB or LBW [26]. None of these studies were adequately powered to determine differences in rates of PTB, or the racial disparities in PTB in medically low risk women across all reproductive ages.

The mechanism by which GPNC may improve birth outcomes is unknown, but existing research suggests that GPNC contributes to positive psychosocial and/or behavioral changes in women [24]. Participation in GPNC has been associated with higher rates of adequate prenatal care, breastfeeding initiation, less excessive gestational weight gain, greater likelihood of using vitamin supplements during pregnancy, improved food security, and more knowledge for prenatal care and more prepared for labor and delivery [17, 19, 23, 25, 27–34]. Qualitative research indicates women generally find GPNC to be a positive experience, meeting many of their preferences for care [17, 19, 35–38]. Although these results are promising, no studies have evaluated whether improving these psychosocial and/or behavioral factors will explain the potential benefits of GPNC on racial disparities in birth outcomes.

The current study addresses the most significant gaps in the current GPNC literature: the lack of a rigorously designed clinical trial to assess the impact for GPNC on PTB and the racial disparity in preterm birth. This study will also measure GPNC’s effects on patient activation, engagement, stress, and health behaviors as they relate to birth outcomes and answer whether improving these maternal psychosocial and behavioral factors will explain the potential benefits of GPNC on birth outcomes or on racial disparities.

### Preliminary research

In 2012, we published a retrospective study of 316 women who participated in GPNC compared with 3,767 women in IPNC [16]. The adjusted odds ratio for PTB for women in GPNC care was 0.53 (95% CI: 0.34, 0.81) as compared to women in the IPNC. The racial disparity in PTB between Black women and White women was also diminished for women in GPNC: the Black-White difference of PTB was 1.0% in the GPNC and 2.4% in the IPNC group. In 2012–2013, we conducted a mixed methods prospective cohort study comparing the effectiveness of GPNC to IPNC on women’s psychosocial health [24, 33]. We recruited 248 women, retaining 89% of participants through pregnancy and 84% into the postpartum period. Women completed surveys at two points during pregnancy and once in the post-partum period. Among women with inadequate initial social support, GPNC participants scored 3.16 points lower (*P* = 0.03) on a scale of prenatal distress in late pregnancy. Among women with high initial prenatal distress, GPNC participants scored 7.96 points higher (*P* = 0.008) on a measurement of planning and preparation coping in late pregnancy [24].

Preliminary data from our retrospective and prospective studies demonstrate the potential for GPNC not only to reduce PTB, but also to reduce racial disparities in PTB. Our preliminary data also indicates that GPNC improves women’s psychosocial outcomes as well, particularly for those reporting high levels of stress in early pregnancy. By using a RCT design, this proposed study will reduce the possibility of selection bias and influences from potential confounding, and have adequate power to conclusively assess the efficacy of GPNC compared with IPNC on rates of PTB and racial disparities in birth and other outcomes among White and Black women.

### Specific aims and hypotheses

The proposed study will employ a RCT design adequately powered to detect difference in PTB by intervention and race. The study will be conducted in a large prenatal care provider in South Carolina (SC), with historically high PTB rates of 16.4%. The proposed study builds on an established research program focused on assessing the impact of GPNC vs. IPNC on birth outcomes and will investigate the following Specific Aims:

### Specific Aim 1

To compare the rate of PTB prior to 37 weeks gestational age and other selected birth outcomes and pregnancy complications (e.g. birth weight, caesarean section rate) among women who participate in CenteringPregnancy GPNC to their counterparts in IPNC.

#### Study hypothesis 1

Women who participate in GPNC will have a lower rate of PTB and other improved birth outcomes as compared to their counterparts in IPNC.

### Specific Aim 2

To compare the risk difference of PTB and other selected birth outcomes of Black women vs. White women in GPNC to the risk differences of Black women vs. White women in IPNC.

#### Study hypothesis 2

The risk difference of PTB and other selected birth outcomes between Black and White women in the GPNC group is smaller than that in the IPNC group.

### Specific Aim 3

To compare whether women in the GPNC have improved maternal psychosocial (i.e. activation, engagement, stress) and behavioral (i.e. smoking, healthy eating, health practices) outcomes as compared to their counterparts in IPNC and to explore whether improving certain maternal psychosocial and behavioral outcomes will explain the potential benefits of GPNC on racial disparities in birth outcomes.

## Methods/design

### Ethical approval

The study protocol (GHS Pro00043994) was approved by Institutional Review Board (IRB) of the Greenville Health System and Clemson University in June 2015. All the study participants will sign written consenting form before they are enrolled in the study.

### Study design and setting

This proposed study will employ an un-blinded RCT design to assess the efficacy of GPNC compared with IPNC on rates of PTB and racial disparities in birth outcomes among White and Black women. Eligible women will be recruited at the time of entry to prenatal care, and will be followed through delivery and for 12 weeks postpartum. All research activities will be conducted at the Greenville Health System (GHS) Obstetrics (OB) Center and ultrasound unit, located in Greenville, SC. Greenville is part of a metropolitan area with a population of approximately 640,000 people, and is approximately 80% urban and 20% rural [39, 40]. The practice has been serving women in the area for more than 40 years, with an annual delivery volume of approximately 2,750 women. The GHS OB Center first began offering GPNC in 2008, and has maintained annual site approval from the CHI since that time. To date, 3,633 patients have attended Centering groups at this practice.

### Patient population

The target population consists of medically low-risk pregnant women of different races/ethnicities. In our retrospective cohort study published in 2012, our study population in the comparison group included 45.8% non-Hispanic White, 25.5% non-Hispanic Black, 22.2% Hispanic and 6.5% “Other” race/ethnicity [21]. We expect that our current study population will be similar.

To be eligible for this study, women will 1) be between 14–45 years of age, and 2) enter prenatal care before their 20^th^ week of gestation. Study exclusion criteria include 1) medical complications of pregnancy which would preclude prenatal care provision by nurse practitioners or participation in group care (e.g. pre-gestational diabetes, severe chronic hypertension, active pulmonary tuberculosis, massive morbid obesity or severe psychiatric illness), 2) multiple gestation, 3) lethal fetal anomalies, and 4) low literacy. The exclusion criteria were set to limit the study participants as low-risk patients, which is consistent with both the GPNC model design and the scope of medical practice of nurse practitioners/nurse midwives who provide GPNC. Women who have participated in this study in a previous pregnancy will also be excluded, in order to maintain independence. Based on our preliminary data, application of these criteria will result in an estimated exclusion of 10% of women for late entry to care and 8% for pre-existing medical complications. The exclusion criteria will be applied to all women before randomization. We will track demographic characteristics and reasons for exclusion for women who are ineligible for the study as well as for those who are eligible but decline participation.

### Participant recruitment and screening

We propose to recruit and follow 3,160 (*N* = 1,580 in each group) pregnant women (see section for sample size calculations). Approximately 250 women begin prenatal care at the GHS OB Center each month, and 75% of them will be eligible for the proposed study (180 eligible women per month). The provider will screen all new patients presenting to the practice for prenatal care (at the first prenatal visit) for eligibility and to introduce the study to eligible women. Given our previous recruitment rate of 50%, we estimate that the targeted study sample size will be achieved in 3 years. At the time of the nurse education visit at the GHS OB Center, all patients will be screened for study eligibility based on review of medical records and a series of screening questions answered by the GHS intake nurses. The final eligibility screening will take place after the patient is scheduled with a healthcare provider. This may be the same day, or may be a separate day from the nurse education visit. Once the history and physical exam has been completed, the research nurses will approach eligible patients for study enrollment. Patients will be taken to a quiet space to have the study explained. The enrollment process involves a face-to-face interview with one of the study team for verification of study eligibility and counseling regarding study procedures, potential benefits and risks, prior to obtaining written consent. Recruitment began in July 2016 and will be monitored monthly. Figure 1 describes the flow of participants through the study recruitment and data collection.

**Fig. 1 Fig1:**
[figure not shown]
Flow chart of patient recruitment and follow up

### Randomization and masking

#### Randomization

Women who are eligible for the study will be offered participation. Women who are interested in participation will have the opportunity to ask questions, confirm interest, provide consent, undergo group assignment, as well as complete the baseline data collection (Survey 1). Women who agree to participate will be randomized 1:1 to IPNC or GPNC based on computer-generated group assignment. These assignments will be stratified by race and ethnicity (Black, White, Hispanic, Mixed, and Other).

#### Masking

Due to the nature of the intervention, it is not possible to blind the group assignment to the participants and providers, but we will mask the providers to the study data. In addition, we will mask the data analysts regarding the group assignment to reduce bias.

### Interventions

#### GPNC (intervention) group

Women will be grouped with other women who are all due to deliver in the same month, and will receive their routine prenatal care together during ten 2-h group sessions meeting CHI’s established standards for CenteringPregnancy. Women will receive a patient notebook for their health information, educational materials, and activities to promote goal setting and self-care. During the first 30 min of each group session, women will measure and record their own weight and blood pressure, and then a credentialed healthcare provider (nurse practitioner, nurse midwife, or physician) will conduct a brief physical assessment in a semi-private area of the group space. Following the individual health assessments, the healthcare provider and a co-facilitator will lead the group discussion for the remaining 60–90 min of each session. Topics discussed throughout sessions include pregnancy and nutrition, childbirth preparation, exercise, stress management, relationships, and parenting (see Table 1). Women randomized to GPNC will have access to additional IPNC visits (outside of the ten scheduled group sessions) as needed to address complications that may arise between group sessions. The GPNC curriculum is designed to be culturally appropriate and the study site will deliver the intervention in both English and Spanish.

#### IPNC (control) group

Women will receive standard, traditional individual prenatal care in accordance with the schedule of visits recommended by the American College of Obstetricians and Gynecologists [41]. Women will attend monthly visits for the first 28 weeks of pregnancy, every two to three weeks until 36 weeks gestational age, then weekly until delivery. Visits will include ongoing physical assessment as well as patient education on common complications of pregnancy, childbirth preparation, breastfeeding, and other relevant topics as needed. Women randomized to IPNC will not attend GPNC sessions.

#### Both groups

Women will receive routine medical screenings as well as specialized tests, interventions, and referrals depending on risk factors and the course of pregnancy [41]. Women with a history of previous preterm birth who qualify for progesterone treatment will receive it [42].

### Compliance, cross-over, and follow-up

Aspects of prenatal care provision and participation will be assessed through medical record review and patient surveys, to measure compliance of both groups, including detailed data for each participant’s use of prenatal care services.

Women who have a miscarriage or leave the practice and deliver their baby at a different hospital system will be treated as lost to follow-up in the final analysis. However, we will make every effort to obtain data for women who deliver at other facilities by requesting medical records when we know the location of delivery, and by obtaining their birth outcomes data through the vital statistics database with the SC Department of Health and Environmental Control.

No matter the directions and the reasons of cross-over and regardless of the number of missed prenatal care visits, participants will be kept in their original assignments, as the primary analysis follows the intent-to-treatment approach. We will also do a secondary analysis measuring outcomes “as treated,” using patients who attend at least five visits of their assigned model of care.

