### Data collection

For this study, data will be collected at the following 3 time points: 1) At the time of Baseline Visit (8–23 weeks of gestational age), women will undergo group assignment and complete the baseline data collection (Survey 1); 2) After 30 weeks gestational age, research nurses will meet participants prior to or after their prenatal care appointment to administer the second survey (Survey 2); and 3) Postpartum data collection will be conducted after women attend their postpartum visit and consist of medical chart abstraction, and will not require patient contact. The study surveys will be administered electronically. Patients’ medical information will be collected from the electronic medical record (EMR). Regular data review/reports will be generated through the EMR to monitor enrollment, group balance, and the timing of the reminder calls & patient incentives. The overall timeline for study visits and data collection is summarized in Table 2.

**Table 2 Tab2:** Data collection and outcome measurement

	Gestational age <23 week (Survey 1)	Gestational age 30+ week (Survey 2)	12-week Postpartum medical chart review
Birth outcomes and pregnancy complications			
Gestational age at delivery			X
Birth weight			X
APGAR scores			X
Admission to neonatal intensive care unit (NICU)			X
Intrauterine fetal demise			X
Neonatal death			X
Pre-eclampsia			X
Gestational hypertension			X
Gestational diabetes			X
Intrauterine growth restriction			X
Macrosomia (weight >4000 g.)			X
Hospital admission during pregnancy, reason			X
Induction and reason			X
Maternal behavioral and other measures			
Maternal smoking, alcohol and marijuana use	X	X	X
Physical activity, dietary intake, and multivitamin use		X	
Maternal psychosocial measures			
Patient activation measure (PAM)	X	X	
Prenatal planning and preparation coping		X	
Prenatal anxiety, and depressive symptoms	X	X	
Shift and Persist	X		
Discrimination in prenatal care		X	
Stress management		X	
Perceived family support	X		
Support from baby’s father & relationship with baby’s father		X	
Life stressor, financial stressor and housing instability in pregnancy		X	
Perceived stress and neighborhood safety	X		
Everyday discrimination scale	X		
Role of religious on dealing with stress	X		
Adverse childhood experience	X		
Interconception care			
Attendance at postpartum visit			X
Postpartum contraception use			X
Demographics			
Race and ethnicity	X		

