### Study outcomes

*The primary study outcome* is PTB (defined as birth at less than 37 weeks gestation).

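### The five-visit secondary analysis excludes women because they delivered early, so it understates preterm birth in both arms and can bias the comparison between arms in either direction

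*Protocol article*

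**What the plan says.** Under Compliance, cross-over, and follow-up, the protocol states that "participants will be kept in their original assignments, as the primary analysis follows the intent-to-treatment approach". It then adds a secondary analysis, labelled *as treated*, "using patients who attend at least five visits of their assigned model of care". The Analytic plan repeats the intention-to-treat principle for all three aims and says nothing further about the five-visit set. The document gives no gestational-age landmark or time-at-risk adjustment for it.

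The primary outcome (Study outcomes) is birth before 37 weeks. The visit calendars are:

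- **GPNC:** "ten two-hour group sessions which take place through the second and third trimesters". Table 1 puts session 1 at 12–16 weeks and session 5 at 26–30 weeks.
- **IPNC:** "Women will attend monthly visits for the first 28 weeks of pregnancy, every two to three weeks until 36 weeks gestational age", then weekly to delivery.
- **Extra visits:** "Women randomized to GPNC will have access to additional IPNC visits". Read literally, these are not visits of the assigned model.

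The abstract admits women who "enter prenatal care before 20 6/7 weeks of gestational age", and Data collection places the baseline visit and assignment at 8–23 weeks.

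**The concern.** Membership of the analysis set depends on a count that accrues after randomisation and that delivery cuts short. When the outcome is early delivery, the outcome partly decides who is analysed. A poor attender who reaches term can still collect five visits. An equally poor attender who delivers at 30 weeks usually cannot.

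The arms also collect visits on different calendars, so the share of preterm births removed need not be equal. The comparison could then show benefit or harm where there is none.

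This is the only adherence-based analysis the protocol describes. If attendance is poor and the intention-to-treat result is null, readers will turn to it.

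**Working it through.** **1. The plan's own figure.** The protocol gives no figure for the five-visit analysis. The nearest is the Aim 1 sample size, used below only for scale. With p0 = 0.13, p1 = 0.13 × 0.70 = 0.091, two-sided alpha 0.05 and 90% power:

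n = [1.96·√(2 × 0.1105 × 0.8895) + 1.2816·√(0.13 × 0.87 + 0.091 × 0.909)]² / 0.039² = 1,356 per group, as stated.

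**2. Earliest fifth visit with none missed.** GPNC windows come from Table 1. IPNC visits are every 4 weeks to 28 weeks, every 2–3 weeks to 36, then weekly. For example, entry at 8 weeks gives visits at 8, 12, 16, 20 and 24.

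| Entry week | IPNC, entry visit counted | IPNC, entry visit not counted | GPNC |
|---|---|---|---|
| 8 | 24 | 28 | 26–30 |
| 12 | 28 | 30–31 | 26–30 |
| 16 | 30–31 | 32–34 | 26–32 |
| 20 | 32–34 | 34–37 | 28–34 |

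The GPNC ranges at 16 and 20 weeks allow for joining at either of two sessions. Each missed session moves the GPNC limit later: one missed gives 28–32 weeks, two 30–34, three 32–36, four 34–38, five 36–40.

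With no missed visits, nearly all of these limits lie below 37 weeks, so a birth before the limit is both preterm and ineligible. With entry at 8 weeks and the entry visit counted, IPNC reaches five visits first. With entry at 16–20 weeks GPNC often does. The two overlap at about 10–12 weeks.

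**3. Effect with no true difference.** Let p = 0.13 in both arms. Let s be the proportion by which retention of women with preterm births falls short of retention of women with term births. Then

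retained PTB = p(1 − s) / (1 − p·s).

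The documents give no gestational-age distribution of preterm births and no attendance rates, so s is an assumption:

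| s GPNC | s IPNC | PTB GPNC | PTB IPNC | Risk ratio |
|---|---|---|---|---|
| 20% | 20% | 10.7% | 10.7% | 1.00 |
| 10% | 5% | 11.9% | 12.4% | 0.95 |
| 20% | 10% | 10.7% | 11.9% | 0.90 |
| 30% | 10% | 9.5% | 11.9% | 0.80 |
| 10% | 30% | 11.9% | 9.5% | 1.25 |

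For 20% versus 10%: 0.104/0.974 = 0.1068 and 0.117/0.987 = 0.1185. With 1,356 per arm the difference of 0.0117 has standard error 0.0121, so the two-sided test rejects about 16% of the time instead of 5%. For 30% versus 10% it rejects about 52%. The retained set would be smaller than 1,356 per arm, which lowers these rates somewhat.

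**4. Null simulations on the two calendars.** PTB was set at 13% in both arms, with an assumed spread of preterm births by week. Retained PTB fell to about 3–12%. The GPNC/IPNC risk ratio was:

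- 0.94–1.04 with entry at 8–13 weeks, equal attendance of 60–90% and the entry visit counted;
- about 1.07–1.26 with entry at 10–19 weeks, equal attendance and the entry visit counted;
- about 0.7 with attendance of 60% in GPNC and 90% in IPNC;
- from about 1.4 up to 2.5 with entry at 10–19 weeks, equal attendance and the IPNC entry visit not counted.

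These show sensitivity to inputs. They are not estimates for this trial.

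**5. The label.** An as-treated analysis classifies women by the care they received. Here a woman who changes model before her fifth assigned-model visit is left out, so the set is closer to per-protocol.

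**The case against.** The strongest reply is that the difference between arms is not fixed by the documents. It depends on entry week, attendance and the counting of the intake visit. If preterm births are lost in equal shares, the risk ratio stays at 1.00, and with early entry and equal attendance it stays close to 1.00. This stands: the lowering of PTB within each arm follows from the rule, whereas the bias between arms is possible but conditional.

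The analysis is also openly secondary, and the sentence that names it defines the set, so nobody is misled about who is in it. That limits the harm but does not remove the selection. For Survey 2 measures, taken after 30 weeks, women must already be undelivered, so the problem is weaker there.

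Three stronger readings are tempting and not supported:

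- *The primary result is compromised.* It is not. Intention-to-treat keeps women regardless of missed visits.
- *The rule favours GPNC, or by a known amount.* Neither direction nor size can be derived from the document.
- *All cross-overs are dropped.* A woman who changes model after five assigned-model visits stays in. Only those who change earlier are excluded.

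**Conclusion.** The concern holds for PTB and other gestation-linked outcomes in this secondary analysis. The five-visit rule selects on the outcome, and this follows from the stated rule and schedules alone. PTB among retained women is understated in both arms. The comparison between arms can be biased in either direction with no true effect: risk ratios run from about 0.7 to well above 1.25 under assumed inputs, and are near 1.0 under favourable ones. The size rests on the assumed timing of preterm births, entry weeks, attendance and counting convention. As defined, the analysis is not a sound basis for supporting or questioning the intention-to-treat result on PTB. It should be changed, but the trial's main conclusion does not depend on it.

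**What to change.** For PTB and other gestation-linked outcomes, replace the five-visit set with a complier-average causal effect. Use randomised assignment as the instrument and define receipt as starting GPNC. In its simplest form this is the intention-to-treat risk difference divided by the difference between arms in the proportion who start GPNC. It excludes nobody for delivering early. State the assumption that assignment affects the outcome only through starting GPNC. Also state that the result is the effect of starting GPNC, not of five or more sessions.

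If the dose question is wanted, add a landmark analysis at one gestational week common to both arms:

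- Include only women undelivered at the landmark, count attendance up to it, analyse PTB after it, and adjust for baseline covariates.
- Set the landmark late enough for several scheduled visits after the latest assignment at 23 weeks. A landmark at 24 weeks would not do, because Table 1 places only sessions 1–3 by then.
- State whether the intake visit counts, and label the analysis observational.

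Rename the analysis so that the label matches the set.

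The cost is plan wording and modest programming. Under Prenatal care process evaluation, visit number, visit type and timing of entry are already to be collected. The downsides are a wider confidence interval, a changed estimand and, in the dose analysis, the loss of births before the landmark.
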